## Abstract

**Background:**

Black sexual minority men (BSMM) are disproportionately affected by HIV. Los Angeles County (LAC) carries a substantial burden of the HIV epidemic in California. Negative effects of both psychosocial and structural barriers highlight the timely need to increase HIV treatment among BSMM. Successful HIV interventions based on social media and mobile phone technology have been demonstrated. This protocol describes LINX LA, a study that tests LINX, a web-based mobile app that provides tailored social services, legal resources, and peer support for BSMM living with HIV (BSMM+) in LAC using a randomized comparison trial.

**Objective:**

During phase 1, the LINX LA study aims to engage in an iterative design process to develop the LINX App using qualitative data to inform and tailor the mobile app technology and its functionality. In phase 2 of LINX LA, we will test the efficacy of the LINX App compared with the LINX App Plus to improve HIV treatment outcomes (ie, antiretroviral therapy adherence, viral suppression) among BSMM+ in LAC by addressing social work and legal needs and developing a forum for peer support.

**Methods:**

In this study funded by the California HIV/AIDS Research Program, we will recruit and enroll BSMM+ participants (aged ≥18 years) in LAC (N=400) to participate in a 12-month study that includes access to the LINX App, which provides a forum for peer support and tailored content aimed at improving the use of social and legal resources. All participants will also receive survey-based interviews at 3 time points (at baseline and 6- and 12-month intervals) and weekly text message surveys that assess medication and treatment adherence. Treatment adherence and viral suppression will be extracted from medical record data. Half of the participants will also be randomly assigned to receive 3 individualized coaching sessions (at 1-, 3-, and 6-month intervals) and the ability to directly message their coach via the LINX App. Over the course of the study, LINX App participants will receive a minimum of US $130 in cash and LINX App Plus participants will receive a minimum of US $190. We hypothesize that participants enrolled in LINX App Plus will demonstrate greater improvement in HIV outcomes compared with LINX App participants.

**Results:**

The LINX study will test the efficacy of a web-based mobile app intervention for BSMM+ in LAC (N=400). The LINX App seeks to increase participants’ knowledge of HIV; to facilitate access to necessary social and legal services, including information and referrals; and to increase social support across participants by providing a mediated forum for engagement.

**Conclusions:**

The implementation of LINX LA aims to develop and test a culturally tailored approach to improve the HIV treatment outcomes of BSMM+.

**International Registered Report Identifier (IRRID):**

PRR1-10.2196/19770

## Introduction

### Background

African American people accounted for 42% of new HIV diagnoses in the United States in 2018 [1]. Black sexual minority men (BSMM) are further disproportionately affected by HIV. BSMM accounted for 26% of new HIV diagnoses and 37% of new diagnoses solely among all sexual minority men (SMM) in the United States in 2017 [2].

In California, the annual number of HIV diagnoses increased by 0.8% from 2013 to 2017; the rate of HIV infection, however, decreased in California during the same period by 2.4% [3]. In 2017, the number of people living in California diagnosed with HIV was 135,082 individuals [3]. Within this group, 73.6% of these individuals were in HIV care and 63.3% of these individuals achieved viral suppression [3]. African American people living with HIV experienced lower rates of HIV treatment engagement in California compared with White, Latino, Asian, and Pacific Islander people [3].

Los Angeles County (LAC) carries a substantial burden on the HIV epidemic in California. In 2017, 31.6% of all newly diagnosed HIV infections in California came from LAC. Of all people living with HIV in California, 38.1% are from LAC [3]. Within LAC, African American people represented 25% of new HIV diagnoses in 2016 [4]. Between 2015 and 2016, the rate of HIV diagnoses decreased for White people in LAC; however, for African American people, the rate of HIV diagnoses increased during the same period [5]. Approximately 84% of all LAC HIV diagnoses in 2016 were among the SMM. Among those newly diagnosed SMM, linkage to and retention in HIV care was less common among African American people than among White, Latino, or Asian and Pacific Islander people [5].

Data on the continuum of care for people living with HIV in LAC in 2016 revealed that 52% of African American people were linked to care, 65% were engaged in care, 49% were retained in care, and 52% achieved viral suppression [5]. These figures, when compared with people living with HIV across California, indicate that LAC’s African American people living with HIV fare worse in terms of HIV outcomes as they have been proportionately less likely to be engaged in care and to achieve viral suppression [3].

Socioeconomic predictors, such as income status, may provide perspective on linkage to HIV care, as African American people experience poverty at a disproportionately higher rate than other racial/ethnic groups in the United States [6]. Poverty is associated with an increased risk of HIV diagnosis among some BSMM, which may also affect the health of BSMM living with HIV (BSMM+) [1] as racism continues to serve as a structural barrier to HIV services for BSMM+ [7]. Black people living with HIV who experience greater racial discrimination were less likely, as documented in prior research, to have an undetectable viral load and a high CD4 cell count [7]. African American people also expressed higher levels of medical mistrust, especially those living with HIV [8]. Higher general medical mistrust is a significant predictor of lower continuous HIV medication adherence over time [9].

Structural racism is related to the decreased likelihood of reporting antiretroviral therapy (ART) use among young BSMM+ [10]. The impact of racism on BSMM+ must be understood in the context of homophobia and HIV-related stigma. BSMM are less likely to disclose their sexual identity or sexual activity to their health care providers compared with SMM from other racial/ethnic groups [11]. These multiple layers of systemic, intersecting oppression and the resulting stigma that BSMM+ face can negatively affect health-seeking behaviors and HIV treatment engagement and highlight the need for tailored interventions for BSMM+.

### Culturally Tailored Mobile App Interventions

HIV interventions that address self-efficacy and resilience are effective in promoting health behaviors [12]. Previous studies highlight strengths-based approaches as appropriate for increasing the use of HIV services by recognizing how BSMM+ overcome challenges to care [12]. Interventions that focus exclusively on risk highlight what is lacking and reinforce harmful stereotypes about individuals facing overlapping stigma [12]. In addition, social support networks are vital to sustain healthy behaviors among BSMM+. HIV interventions that facilitate peer social support build resilience through avenues of emotional and informational support. These social exchanges are opportunities for BSMM+ to empower each other, encourage healthy behaviors, and provide information on HIV-related resources. Such interventions promote resilience processes to combat the negative effects of multiple stigmas, including those related to racial minority identity, sexual minority identity, and HIV status [12,13].

The use of social media and mobile phone technology have been proven to be effective avenues for HIV intervention [12,14,15] because they are widely available and acceptable methods for HIV intervention [16]. Mobile apps and social media platforms allow interventions and information regarding HIV to be more accessible to communities that have been deemed *difficult to reach* due to multiple stigmas [14]. Although these platforms are virtual, community partnership remains essential to maintain sustained engagement and effectiveness as collaboration ensures tailored messaging for key populations such as BSMM+ [12]. In addition, online spaces facilitate social connectivity while giving BSMM+ the ability to remain anonymous, should they choose [12].

Existing technologies, including HIV-focused mobile apps, are available to the public; however, usage remains to be low [17,18]. Technology created to address the needs of people living with HIV focuses specifically on HIV education, access to services (eg, HIV testing, linkage to care), maintaining communication between the patient and provider to support adherence and retention in care, and to support the work of providers [19]. Through its formative work, the LINX web-based mobile app (LINX LA) study identified a gap in existing mobile apps. No health mobile apps at this point focus on the complex structural and psychosocial barriers that BSMM+ face to improve HIV outcomes, including upstream factors such as housing and homelessness, lack of access to public benefits, and other social and legal needs. This study aims to test the efficacy of a web-based platform designed by and tailored for BSMM+ that provides social and legal resources as well as a forum for peer support. First, we hypothesize that participants in the LINX App Plus condition will demonstrate improvement in HIV outcomes as compared with those in the LINX App arm of the study. Second, we hypothesize that by offering social and legal services case management, the study could address 2 primary issues faced by many BSMM+—housing and financial instability.

## Methods

### Overview

The proposed study is a randomized comparison trial of a web-based mobile app titled *LINX*. Participants will be randomly assigned to either the intervention (ie, treatment group) or the comparison group. Those in the intervention group will receive the app and access to a LINX Coach (*LINX App Plus* condition) and those in the comparison group will receive the LINX Mobile app only (*LINX App* condition). Participants in both arms of the study will remain on the mobile app for 12 months. The overarching goal of the study is to evaluate the efficacy of LINX App Plus compared with LINX App to improve HIV treatment outcomes (ie, ART adherence, viral suppression). The research team did not register this study at ClinicalTrials.gov because it did not involve randomization to a true control group. Owing to ethical concerns about withholding the mHealth intervention, all participants received the app; half were randomized to receive coaching.

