### Primary Outcomes

The primary outcomes that the study will measure include the degree to which using the LINX App may impact medication adherence and viral suppression. These primary outcomes were assessed through self-reported data verified through an independent medical chart review. The study will measure how outcomes differ between the LINX App and LINX App Plus conditions and whether the intensity of use of the platform (ie, intervention dosage) is associated with these outcomes.

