**Primary**					
	Technology use		Multiple items		Likert scale, range 1-5
	Medication adherence		Self-reported medication adherence; HIV medical record data		Dichotomous; Yes or No HIV medication adherence or HIV-associated medical appointment
	Viral supression		Viral load and CD4 counts		Continuous

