### Planned Analytic Approach

Descriptive statistics of all measures involved (background characteristics, potential moderators and mediators, and outcomes) will be calculated to inform the bivariate analyses and subsequent statistical modeling. On the basis of the nature of the key outcome measures (continuous, categorical, or binary), we will use a full spectrum of analytical approaches to evaluate the data including analysis of variance, analysis of covariance, linear regression, and logistic (binary or ordinal) regression. With 3 time points, repeated-measures missed effect models will also be applied to model the global fixed effect as well as individual participants’ random variation. Our approach to modeling will be to first examine the raw associations with bivariate analyses and then the adjusted and controlled association. Confounding relationships are evaluated through changes in the regression coefficient. The final models will be selected based on goodness-of-fit measures, such as r-square, likelihood ratio, c-statistics, and analysis of covariance, a penalized likelihood. Estimates of effect will be presented with associated 95% confidence limits and associated *P* values.

Preliminary analyses will describe associations between potential predictor variables between both arms of the randomized controlled trial. The initial focus will be to understand the associations between predictors and specified outcomes and to identify confounding or co-linearity that may impact later analyses. We will also describe correlations across various domains to inform the development of our final comprehensive model. We will develop base models predicting engagement in HIV care from demographic predictors (ie, age, education, income, housing status) to identify demographic variables that will be controlled for (as confounding variables or effect modifiers) when examining associations between intervention effects and outcomes. Analyses will be performed to determine robustness and to understand potential confounding or collinearity between predictors. Testing of significance for independent variables will include Wald chi-square tests for continuous or dichotomous variables and/or global goodness-of-fit tests if polytomous categorical variables are regressed. Estimates of effect will be presented with associated 95% confidence limits and associated *P* values.

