### Expected Timeline

The LINX App was completed and recruitment and enrollment for the trial started in May 2018 on a rolling basis. Owing to the outbreak of COVID-19, the collection of survey data at 3 time points over 12 months will pose a challenge. Nonetheless, the length of the study per patient will be 12 months. We expect to complete data collection 12 months after the last participant has been enrolled in the study, that is, by January 2021, and plan the dissemination of results subsequently.

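### The reason given for not registering the trial does not fit a randomised efficacy comparison, and the article does not fix the deciding outcome because its own outcome statements conflict

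*Protocol article*

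**What the plan says.** On registration, the Overview says: "The research team did not register this study at ClinicalTrials.gov because it did not involve randomization to a true control group". It explains that everyone received the app for ethical reasons and half were randomised to coaching.

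On design, the same section says: "Participants will be randomly assigned to either the intervention (ie, treatment group) or the comparison group". It gives the aim as: "The overarching goal of the study is to evaluate the efficacy of LINX App Plus compared with LINX App to improve HIV treatment outcomes". Target Population plans 200 participants per condition. Planned Analytic Approach refers to "potential predictor variables between both arms of the randomized controlled trial".

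On timing, Expected Timeline reports that "recruitment and enrollment for the trial started in May 2018 on a rolling basis". The article already describes changes made because of COVID-19. The only identifier it shows is the journal's own report identifier, in the Abstract.

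On outcomes, Primary Outcomes concerns "the degree to which using the LINX App may impact medication adherence and viral suppression". Table 1 also places "Technology use" under Primary. Sample Size Calculation and Power Analysis names linkage to HIV care as the main outcome. Statistical Analyses promises an overall type 1 error of .05 through corrections, with Bonferroni and Hochberg as examples.

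**The concern.** Giving the app to both arms makes the comparator an active one. It does not remove the randomised comparison, the between-arm hypothesis or the significance test. The need to fix outcomes before the arms are compared comes from randomising and testing, not from having an untreated arm. The stated reason therefore does not support the decision.

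This would matter less if the article itself settled which App Plus versus App result decides the trial. It does not, because its outcome statements differ. A multiplicity correction can be verified only when the set of tests is known. With several outcomes in print as main or primary, an outside reader cannot tell which result was the planned one, or over how many tests the 5% was to be held.

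**Working it through.** **1. Reason against design.** The Overview gives the lack of a true control group as the reason for not registering. It also describes random assignment to an intervention or a comparison group, with efficacy as the goal. Planned Analytic Approach uses the term randomized controlled trial. The reason and the design description do not agree.

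**2. Outcome statements side by side.**
- Overview and Primary Outcomes: medication adherence and viral suppression.
- Table 1, Primary: technology use, adherence and viral suppression. The adherence variable is yes/no for adherence or an HIV-related appointment. Viral suppression is measured by viral load and CD4 counts and typed as continuous.
- Sample size section: linkage to HIV care, which is neither in Primary Outcomes nor a row of Table 1.

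This puts four candidates in print: adherence, viral suppression, technology use and linkage.

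**3. The plan's own sample size.** Inputs from the sample size section: 70% base rate, 12.5-point difference, α = .05 (taken as two-sided), power 80%, 200 per arm.

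n per arm = [1.960·√(2·0.7625·0.2375) + 0.842·√(0.70·0.30 + 0.825·0.175)]² / 0.125² = (1.1796 + 0.5010)² / 0.015625 ≈ 181.

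With continuity correction this is 197, against 200 stated. The figure reproduces, but for linkage only.

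**4. The same 200 per arm for viral suppression.** This treats suppression as yes/no. Assumed base rate: 52%, which Background gives for all African American people living with HIV in Los Angeles County in 2016. For 52% versus 64.5%, without continuity correction:

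Power = Φ{[0.125·√200 − 1.960·√(2·0.5825·0.4175)] / √(0.52·0.48 + 0.645·0.355)} = Φ[(1.7678 − 1.3669)/0.6918] = Φ(0.579) = 71.9%.

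- Needed for 80% power: 244 per arm (259 with continuity correction).
- Detectable difference at 200 per arm: 13.7 points.
- At the statewide 63.3% in Background: 12.8 points.
- With Bonferroni over two primaries (α = .025) at 52%: (1.7678 − 1.5632)/0.6918 = 0.296, so power is 61.6%. The detectable difference is then 15.1 points (14.0 at 63.3%).

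The article gives no base rate for adherence, so no matching figure is offered for it.

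**5. Size of the exposure if no correction were applied.** For k independent outcomes, all null, each tested at .05, P(at least one P<.05) = 1 − 0.95^k:
- k = 2 (Primary Outcomes): 9.8%
- k = 3 (for example, adding linkage): 14.3%
- k = 4 (adding technology use as well): 18.5%

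Positive correlation between the outcomes lowers all three.

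**The case against.** Several points on the other side stand.

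- **Registry.** The Overview names only ClinicalTrials.gov. A reader might infer that no public record exists at all. The article does not show that: it cites no other registry but excludes none. The article is itself public, and it repeats adherence and viral suppression as the efficacy outcomes in the Abstract, Overview and Primary Outcomes. The record is late and inconsistent, not absent.
- **Error rate.** A reader might take 18.5% as the trial's false-positive rate, or count months 6 and 12 separately to reach 1 − 0.95^8 = 33.7%. Neither is supported. Statistical Analyses commits to a correction, no section makes each visit a separate primary test, and Planned Analytic Approach foresees repeated-measures models over the three time points.
- **Technology use.** Primary Outcomes omits it and treats intensity of platform use as intervention dosage, so it may not have been meant as a rival efficacy result. Table 1 nevertheless labels it primary.
- **Unseen documents.** The deciding visit and the family of tests may be fixed in a full protocol or analysis plan. Their absence here is not the finding. Such a document would still not make the stated reason valid or reconcile the three printed outcome statements.
- **Effect on results.** Non-registration changes no allocation, estimate or test. The statistical weight of the point comes from the conflicting outcomes, which would need correcting even in a registered trial.

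**Conclusion.** The point holds in a limited form. The reason for not registering does not fit the design that the article describes. Within what is shown, nothing fixes the deciding App Plus versus App outcome, because Primary Outcomes, Table 1 and the sample size section disagree. The promised 5% overall error rate therefore cannot be checked from this article. The 9.8%, 14.3% and 18.5% figures show what is at stake under independence and without correction; they do not describe the plan.

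The choice of outcome also affects power. The stated 80% for 12.5 points reproduces for linkage but does not carry over to viral suppression at an assumed 52%, where it is about 72% before any correction. That rate comes from a broader population than the trial's, so the figure is illustrative. The article does not show that outcomes were switched or that results had been seen by arm.

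**What to change.** 1. **Overview:** keep the statement that the trial was not prospectively registered, and remove the rationale. Deleting the whole sentence would lose a useful disclosure.
2. **Registration:** register as a two-arm randomised trial of App Plus versus App, labelled retrospective with enrolment from May 2018. State whether any outcome had already been examined by arm. Preferably do this before any such comparison; the article does not establish whether that is still possible.
3. **Outcomes:** make Primary Outcomes, Table 1 and the sample size section agree on adherence and viral suppression, each with one definition, one source and one time point. Move technology use and linkage to secondary or exploratory.
4. **Multiplicity:** apply the correction promised in Statistical Analyses across these two primaries, and name the method.
5. **Sample size section:** restate power, or the detectable difference, for the primary outcomes instead of linkage, with the assumed base rates shown.

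Registration itself is light administrative work. Reconciling the outcome definitions and redoing the power statement takes more effort. The trial must disclose late registration and a less favourable power figure: in the 52% illustration, about 72% for 12.5 points, or about 62% with Bonferroni over two primaries.

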### Target Population

The goal of the study is to recruit a minimum of 400 participants for the study. Half of the sampling group (200 individuals) will be randomly assigned to the LINX App condition and the other half will be assigned to the LINX App Plus condition (Figure 1). To be eligible for the study, participants must be aged at least 18 years old or older and must be male, Black or African American, and gay, bisexual, or other sexual minority. Participants must also own a smartphone, be living with HIV, reside in LAC, and be able to provide informed consent.

